**ActiGraph (GT3X+)**		
• Time in light physical activity (min)	✓	✓
• Time in moderate physical activity (min)	✓	✓
• Time in vigorous physical activity (min)	✓	✓
• Time in MVPA in 10-min bouts (min)	✓	✓
• Counts per minute	✓	✓

#### Process evaluation

In alignment with the Medical Research Council guidelines on evaluating complex interventions [38], the RCT is accompanied by a systematic and rigorous process evaluation to gain an understanding of how sit-stand workstation interventions work in practice [44]. Process evaluations are particularly important in multi-site interventions to explore differences in implementation and outcomes [45].

##### Activity diaries

Activity diaries will be used to determine the type and context of active and inactive behaviours, to facilitate understanding of the factors that influence sitting, standing and physical activity in the workplace context. Participants will be asked to record the behaviour that they spent the most time doing during each hour, during each 7-day objective data collection period. A text message, reminding participants to complete their activity diary, will be sent to participants once daily throughout each data collection period. Text message models have shown success in increasing compliance to data collection [46].

##### Ethnographic participant observation

This method will be used to understand organisational culture, placing importance on the perceptions of the people under study within their usual environment [47]. The ethnographic participant observation will provide insight into the context within which the intervention is taking place; this will elicit understanding of the feasibility and acceptability of sit-stand workstation interventions, and the social processes that underpin use of the sit-stand workstations and physical activity in the workplace. The participant observation involves the lead researcher taking a volunteering role within the participating organisations. There will be three observation phases within each worksite; before the installation of sit-stand workstations, 4–5 months following the installation of sit-stand workstations, and 10–11 months following the installation of sit-stand workstations. The lead researcher will spend approximately 12 full working days at the workplace during each phase, engaging in work tasks related to physical activity and/or workplace health, set by the volunteering organisation.

##### Key stakeholder and participant interviews

Qualitative interviews will enable explorations of perceptions and meaning to increase understanding of a particular phenomenon [48]. Thus, interviews will be used within this study to delineate the perceptions of both key stakeholders and participants in relation to sit-stand working and physical activity in the workplace, to understand the factors that influence the success (or otherwise) of the sit-stand workstation intervention in influencing sitting and physical activity. Specifically, interviews with participants will explore processes that influence use of sit-stand workstations, such as experiences of standing, relationships with other employees and working identities, and will last approximately 60 minutes. These will take place with 12 participants at two time points; 7-months and 12-months following the installation of sit-stand workstations. Interviews with key stakeholders and decision makers in the implementation process from the participating organisations, will elicit understanding of the feasibility, acceptability and sustainability of the sit-stand workstation intervention. Interviewees will include staff working in employee wellbeing, human resources, IT, health and safety, and facilities, as well as estates personnel and senior directors. Approximately ten stakeholders from each organisation will engage in 45 minute telephone interviews, within two months of sit-stand workstations being installed.

### Sample size

A formal power analysis to determine sample size was not conducted as the threshold for meaningful reductions in sitting is unknown. The proposed sample size of the present study (N = 30) is similar to previous pilot studies utilising sit-stand workstations in office environments that have reported significant changes in outcomes related to sitting, standing and stepping e.g. [35,49,50].

### Data analysis

#### ActivPAL3™

The monitor records the exact duration of each bout of sitting (or lying), standing, and stepping. Data will be downloaded and processed further using ActivPAL3™ proprietary software, PAL Analysis 7.

#### ActiGraph GT3X+

Activity counts will be recorded at 1-second intervals. Data will be downloaded and processed using proprietary software, ActiLife 6. Time spent in light, moderate and vigorous activity will be calculated by classifying vector magnitude counts according to the cut-points developed by Troiano; light activity is considered 101 to 2019 counts per min, moderate activity is considered 2020 – 5998 counts per min, and vigorous activity ≥5999 counts per min. These cut-points have been validated in the general adult population [51].

#### Non-wear time criteria

ActiGraph GT3X+ non-wear criteria will be developed based on acceptable standards and examination of the data, as different criteria have been shown to impact the final sample size and outcome variables [52]. By comparing the ActiGraph GT3X+ to the ActivPAL3™ output, it will be possible to ascertain which criteria are most accurate for the data set.

#### Qualitative data analysis

Brief ethnographic field notes will be recorded throughout the day during the participant observation phases, with expanded field notes being written at the end of each day of participant observation. All interviews will be recorded using an Olympus LS-11 Dictaphone and transcribed ad verbatim. Qualitative data will be analysed using thematic content analysis via NVivo 10 software. Thematic analysis reports detail-rich data by identifying, analysing and interpreting patterns within the data [53]. Analysis will initially involve reading and re-reading the field notes and transcripts to become fully immersed in “the details and specifics of the data” to allow unearthing of patterns, themes and interrelationships ([54] p.362). Data will then be coded before searching for, identifying, reviewing and defining themes [55].

### Statistical methods

Two-way repeated measures ANCOVA will be conducted using IBM SPSS Statistics 20 to compare the outcome measures between study arms and across the intervention (between data collection time points). Relevant covariates will be controlled for, including body mass index.

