#### Participant selection

Of the potential participants that attend a recruitment workshop and complete the expression of interest form, those that do not meet the eligibility criteria will be excluded immediately. Thirty participants will then be selected strategically to take part in the research; selection will ensure the sample is representative of the range of characteristics on the expression of interest form (see above). The participants that are not selected will be put on a waiting list in case of drop-outs.

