### Randomisation

Participants will be allocated randomly to one of three arms using an online randomisation programme (www.randomizer.org). Participants from the two participating organisations will be randomised separately, to achieve an equal number in each study arm in both organisations. Given the nature of the intervention, i.e. the fact that participants may or may not receive a sit-stand workstation, it will not be possible to blind participants or researchers to arm allocation. However, concealment allocation will be implemented [27].

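### The only named analysis, repeated-measures ANCOVA, as ordinarily run discards anyone with one missing visit; a mixed model would keep the observed data of all 30 participants

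*Protocol article*

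**What the plan says.** The Statistical methods section of the protocol article has two sentences. The first names the model, the software and the comparison: "Two-way repeated measures ANCOVA will be conducted using IBM SPSS Statistics 20 to compare the outcome measures between study arms", and also across the data collection time points. The second adds covariates: "Relevant covariates will be controlled for, including body mass index". No other quantitative analysis is named, so this model serves every primary and secondary outcome.

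Study design sets five measurement points: baseline, 2 weeks, 3, 6 and 12 months. Outcome data makes each a seven-day wear period, with one monitor on the thigh and another on the hip. Sample size gives the total, justified by similarity to earlier pilots: "The proposed sample size of the present study (N = 30) is similar to previous pilot studies utilising sit-stand workstations in office environments". It also states: "A formal power analysis to determine sample size was not conducted as the threshold for meaningful reductions in sitting is unknown". Randomisation forms three arms, with the aim: "Participants from the two participating organisations will be randomised separately, to achieve an equal number in each study arm in both organisations".

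The article gives no expected attrition. It leaves the hip monitor's non-wear rule to be developed from the data and acknowledges that such rules affect the final sample size.

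**The concern.** Classical repeated-measures ANCOVA works on a complete vector of outcomes per person. A participant with four valid weeks and one invalid week therefore contributes nothing to that outcome, and a missing body mass index has the same effect. With about 10 people per arm and five week-long recordings spread over a year, a modest failure rate per visit adds up.

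Two things are at stake. The first is precision: valid recordings are collected and then discarded. The second is bias. Participants know their arm and only two arms receive a desk, so loss may differ by arm. If it also depends on how much people were sitting at earlier visits, those with complete data are a selected group and the arm contrast among them can be distorted.

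**Working it through.** **Inputs from the protocol article.** N = 30 (Sample size); three equal arms (Randomisation), so 30/3 = 10 per arm; five visits (Study design), so 30 × 5 = 150 planned person-visits. N = 30 cannot be re-derived, because the article says no power calculation was made.

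**Assumptions, none of them in the article.** Missingness rates; two-sided alpha of 0.05; 80% power for detectable differences.

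**Step 1: who remains.** If each visit is missing independently with probability m, expected complete cases are 30 × (1 − m)^5. The method uses 150 × (1 − m)^5 of the 150 × (1 − m) person-visits observed. If the only loss is permanent dropout d, spread evenly over the four follow-up visits, complete cases are 30 × (1 − d). Each leaver then loses (4 + 3 + 2 + 1)/4 = 2.5 visits on average, so 150 − 30 × d × 2.5 person-visits are observed and 150 × (1 − d) are used.

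| Assumed loss | Complete cases of 30 | Per arm | Person-visits observed | Person-visits used |
|---|---|---|---|---|
| 5% per visit | 23.2 | 7.7 | 142.5 | 116.1 |
| 10% per visit | 17.7 | 5.9 | 135.0 | 88.6 |
| 15% per visit | 13.3 | 4.4 | 127.5 | 66.6 |
| 20% per visit | 9.8 | 3.3 | 120.0 | 49.2 |
| 10% dropout only | 27 | 9 | 142.5 | 135 |
| 20% dropout only | 24 | 8 | 135.0 | 120 |
| 30% dropout only | 21 | 7 | 127.5 | 105 |

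A mixture lies between: 15% dropout plus 5% intermittent missingness leaves 30 × 0.85 × 0.95^5 = 19.7, and with 10% intermittent missingness 30 × 0.85 × 0.90^5 = 15.1. At 10% per visit, (135.0 − 88.6)/135.0 = 34% of the recordings obtained would go unused.

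**Step 2: precision.** For one pairwise comparison at one visit, unadjusted (two-sample noncentral t), the difference detectable with 80% power is 1.32 SD at 10 per arm, 1.41 at 9, 1.51 at 8, 1.80 at 6 and 2.38 at 4. At 10% per visit about 9 per arm would be seen at 12 months (10 × 0.9), but only about 6 would have all five visits. Deletion then moves the detectable difference from about 1.41 to about 1.80 SD. Under permanent dropout alone, the people seen at 12 months are the complete cases, so deletion costs no one at that visit; what is lost is the leavers' earlier recordings.

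**Step 3: bias.** An illustrative simulation assumed no true effect, a correlation of 0.6 between visits, and dropout in the intervention arm that rises with sitting at the previous visit. About 72% completed. The 12-month contrast among completers was off by about 0.19 SD in favour of the intervention, while the contrast with no data lost was unbiased. This shows that bias can arise; it does not predict its direction or size here. The mixed model was not run in this simulation. The case for it is that this dropout depends only on observed earlier values, which is missing at random.

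**The case against.** The strongest reply is that listwise deletion is inferred. The article is condensed, does not name the SPSS procedure and gives no missing-data rule; an analysis plan that is not shown could impute before the ANCOVA. That is fair, and silence on missing data is not the point here. The point is that the one model named handles incomplete visits badly as ordinarily run, and a better one is available for a change of wording.

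Other parts of the reply also stand:

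- Independent missingness is pessimistic, since missed visits tend to cluster in the same people. The dropout-only rows are much milder, and eligibility excludes people who plan to leave or to be away for four weeks or more.
- The two monitors feed different outcomes, so losing one removes only its own outcomes.
- Complete-case analysis does not always need data missing completely at random. With a correct model it is also valid if loss depends only on arm and included covariates.
- The study calls itself a pilot and claims no power.

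A reader might go further and infer that randomised participants who leave will be replaced by people who were not randomised with the rest, because of this sentence: "The participants that are not selected will be put on a waiting list in case of drop-outs". The document does not support that. The sentence stands under Participant selection, directly before Randomisation, and concerns people not chosen among the thirty. Nothing says that a randomised participant is replaced or that a newcomer takes a vacated place.

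**Conclusion.** The concern holds as a should-fix. The named method, in its ordinary form, would exclude from each outcome everyone without five valid visits and complete covariates. The counts are exact arithmetic on assumed rates: 23 to 10 of 30 under independent missingness of 5% to 20% per visit, and 27 to 21 under dropout alone of 10% to 30%. Since the article gives no rate, the loss cannot be called severe as a matter of fact, nor can bias in a particular direction be asserted. Waste of observed data follows whenever anyone has an incomplete record and nothing is imputed. Bias follows if loss depends on arm and earlier sitting. Neither conclusion rests on the waiting list.

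**What to change.** Replace the repeated-measures ANCOVA with a linear mixed model for the four post-baseline visits. Terms: arm, visit, arm-by-visit interaction, baseline value of the outcome and organisation, with body mass index kept if wanted. Fit by REML with Kenward-Roger or Satterthwaite degrees of freedom. Use all available visits of all randomised participants, in the arm to which they were allocated.

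State the assumption: the model is valid under missing at random and is itself biased if missingness depends on current values that are not seen. A short sensitivity analysis should address that case. State too how a missing baseline or covariate value is handled, because with baseline as a covariate that person would otherwise still drop out.

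The cost is wording only, with no extra participants or measurements. Trial status says data collection was still under way at submission, so the change could be made before the final analysis. The one small downside is that a covariance structure must be chosen in advance; at this sample size a simple one such as compound symmetry should be named as fallback in case a richer one does not converge.

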## Methods/Design

### Study design

An RCT comparing the effects of a sit-stand workstation only and a multi-component sit-stand workstation intervention, with usual office-based working practice (no sit-stand workstation) will be implemented. The study will be conducted with office workers across two organisations according to Cochrane recommendations [30], with ‘individuals’ being the unit of randomisation. The design employs two intervention arms: (1) a multi-component sit-stand workstation intervention (SS-MC); and (2) sit-stand workstation only (SS-O). A control arm (CG) for usual desk-based working practice (no sit-stand workstation) will also be included. Objective data collection will take place at 5 time-points over the course of 12-months: baseline (approximately one month before desk installation), and then post-installation at 2-weeks, 3-months, 6-months and 12-months. See Figure 1 for an overview of the study design and major study components. Ethics approval has been granted by Brunel University London local research ethics committee. All participants will receive a participant information sheet, which details their ethical rights, and provide written informed consent. The conduct of this study will follow the CONSORT guidelines (http://www.consort-statement.org/).

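### The analysis names BMI but neither the randomisation stratum nor the baseline outcome, and as naturally read counts baseline as a fifth time level; adjusting for both would gain precision at almost no cost

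*Protocol article*

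**What the plan says.** Three parts of the Protocol article bear on this.

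- **Randomisation.** "Participants from the two participating organisations will be randomised separately, to achieve an equal number in each study arm in both organisations". Organisation is therefore a stratum with two levels.
- **Study design.** "Objective data collection will take place at 5 time-points over the course of 12-months: baseline", followed by 2 weeks, 3 months, 6 months and 12 months after installation. Baseline is counted among the five time points and precedes installation by about a month.
- **Statistical methods.** A two-way repeated measures ANCOVA is to "compare the outcome measures between study arms and across the intervention (between data collection time points"). On covariates the text says: "Relevant covariates will be controlled for, including body mass index".

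BMI is the only covariate named. The text does not say whether baseline is a time level or a covariate, or whether the arm main effect or the arm-by-time interaction is the test of the intervention.

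**The concern.** Read together, the Study design and Statistical methods sections suggest a model with arm as one factor and five time points, baseline included, as the other. That reading raises two matters.

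First, a main effect of arm taken over all five levels averages in a visit made before any workstation was installed, when the arms can differ only by chance. If the interaction or a change contrast is used instead, the dilution goes. Baseline is then subtracted in full rather than weighted by how well it predicts follow-up, which is less efficient.

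Second, stratifying by organisation balances it across arms. If organisation predicts the outcome and is left out of the model, its variation stays in the error term although it no longer contributes to the error of the arm comparison. Standard errors then come out larger than they need be.

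What is at stake is precision. With 30 participants in three arms there is little to spare, and both variables are recorded anyway.

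**Working it through.** **Inputs from the article.** N = 30 (Sample size); three arms, randomised equally within each of two organisations (Randomisation); five time points, one before installation (Study design). This gives 30/3 = 10 per arm, and 5 per arm per organisation if the organisations contribute 15 each (assumed).

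**Assumed inputs.** There is no power figure to reproduce: "A formal power analysis to determine sample size was not conducted as the threshold for meaningful reductions in sitting is unknown". The within-person correlation (r, taken as equal between all visits), the outcome SD, the size of the effect and the influence of organisation are all assumptions, so ranges are shown.

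**1. Arm main effect with baseline as a level.** With a constant effect d after installation and none before, the expected main effect is (0 + d + d + d + d)/5 = 0.8d. The arm-by-time interaction is not reduced.

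**2. Average effect over follow-up, three ways.** In SD units, the variance per participant is:
- main effect over five levels: (1 + 4r)/5, estimating 0.8d;
- mean of four follow-ups minus baseline: (1 + 3r)/4 + 1 - 2r, estimating d;
- mean of four follow-ups adjusted for baseline: (1 + 3r)/4 - r², estimating d.

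The SE of a two-arm contrast is √(2 × variance/10). At r = 0.5 the variances are 0.600, 0.625 and 0.375, so the SEs are 0.346, 0.354 and 0.274. Power for d = 1 SD (two-sided 5%, noncentral t, 27, 27 and 26 degrees of freedom):

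| r | Five-level main effect | Change from baseline | Baseline-adjusted |
|---|---|---|---|
| 0.3 | 73.9% | 63.5% | 93.4% |
| 0.5 | 60.5% | 77.8% | 94.0% |
| 0.7 | 50.8% | 94.0% | 98.1% |

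The last column is best throughout. Its advantage over the change contrast shrinks as r rises.

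**3. A single follow-up visit.** Change from baseline has variance 2(1 - r) and the adjusted value 1 - r². The ratio is (1 + r)/2:
- r = 0.4: 0.84/1.20 = 0.70, or 30% lower with adjustment;
- r = 0.6: 0.64/0.80 = 0.80, or 20% lower;
- r = 0.8: 0.36/0.40 = 0.90, or 10% lower.

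**4. Leaving out organisation.** Let R² be the share of the remaining variance that organisation explains. With balanced cells, the interval without it, relative to the interval with it, is t(27)/[√(1 - R²) × t(26)]. Type I error was simulated with 20,000 runs and 5 per cell.

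| R² | Relative width without organisation | Type I error without | Type I error with |
|---|---|---|---|
| 0 | 1.00 | – | – |
| 0.1 | 1.05 | 4.2% | 5.4% |
| 0.2 | 1.12 | 2.7% | 5.0% |
| 0.3 | 1.19 | 1.8% | 5.0% |

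**5. When organisation adds anything beyond baseline.** Mean simulated SEs for one follow-up visit, in minutes, with SD 80, r = 0.6, 10 per arm and an assumed 60-minute gap between organisations:
- gap appears only after baseline, baseline-adjusted: about 32.3 without organisation and 28.9 with it, so 32.3/28.9 = 1.12;
- same gap already present at baseline, baseline-adjusted: about 29.2 and 28.9, a difference of about 1%;
- same gap already present at baseline, change contrast: about 31.6 either way, because a stable gap cancels;
- no gap, baseline-adjusted: about 28.9 either way.

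**The case against.** The strongest reply is that the article does not make the choices it might be criticised for. Its covariate sentence is open-ended, so organisation and the baseline value are unnamed, not excluded. Comparing outcomes across the intervention could mean the four post-installation visits, and an ANCOVA with an open covariate list leaves room for baseline as a covariate. A fuller protocol or analysis plan may settle both. This stands in part: a reader might infer that the trial will omit its stratum and treat baseline as a repeated level, but the text proves neither. The five-level reading is only the natural one, since the article counts baseline among its data collection points.

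A reader might also infer that the planned test understates the effect by a fifth. That does not follow. The 4/5 factor belongs to the arm main effect alone. The same two-way model yields the arm-by-time interaction, which is undiluted, and the article does not say which of the two is the test.

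Lastly, one might infer that omitting organisation gives a wrong or materially underpowered comparison. The documents do not support this either. Allocation is balanced within organisation, so omission causes no bias and any error is on the conservative side. A gain of the order of 12% in SE needs a gap between organisations that emerges only after baseline. The article gives no figure for any gap. It does expect organisational culture to matter for sitting and activity, which is a reason to include the term but not evidence of its size.

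**Conclusion.** The point holds as a free improvement. The article specifies an arm-by-time model and picks out BMI, while the two variables its own design brings forward, the stratum and the baseline outcome, go unnamed.

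The firmer gain is from baseline. If follow-up is compared with baseline by change, covariate adjustment cuts the variance of a single-visit contrast by 10% to 30% over r = 0.8 to 0.4. If instead the arm main effect over five levels were the test, it would estimate only 4/5 of the average follow-up effect.

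The gain from organisation is conditional. It is nil if organisation adds nothing beyond baseline, and intervals without it are 5% to 19% wider at a residual R² of 0.1 to 0.3. Including it also keeps the test near its nominal level when organisation is prognostic.

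All these sizes rest on an assumed correlation, an assumed organisation effect, complete data and equal cells. The 4/5 factor needs only a five-level main effect and no expected arm difference at baseline.

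**What to change.** In Statistical methods, state that the four post-installation visits are the repeated levels and that the model contains arm, visit, arm-by-visit, the baseline value of the same outcome, and organisation. BMI can stay as an optional further covariate. Estimate the arm contrasts at each visit from this model. If a separate analysis plan already specifies this, a sentence saying so is enough.

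The cost is one or two degrees of freedom, set against 27 between participants in a model with arm alone. No new data are needed, because organisation is known at randomisation and every outcome is measured at baseline.
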